#### Cost-Effectiveness Analyses

The cost-effectiveness of implementing the intervention will be determined from two perspectives: (1) the Ministry of Health and Long-Term Care (MoHLTC) (Canada) and (2) society (Canada and the United Kingdom) (see Table 3). Separate analyses will be conducted from each perspective. MoHLTC costs will include costs associated with health service utilization over the study period (eg, hospitalization, emergency room visits, day surgery or procedure, laboratory services, outpatient visits, prescription drugs, and home care services from the Institute of Clinical Evaluative Sciences). Time that health providers (eg, pharmacists) spent on the SMArTVIEW portal will be calculated by multiplying the time with unit costs from standard costing sources in Ontario. From the societal perspective, costs will include those from the MoHLTC perspective, including costs incurred to patients and family members (eg, travel cost and productivity loss), which will be captured through the AHCR.

The first economic analysis outcome is the incremental cost of the intervention compared to usual care. We will analyze the total cost as a dependent variable, using a regression model to estimate the difference in expected health care cost between the two groups. The intervention will be the primary independent variable and the regression model will adjust for potential confounding variables. In theory, an ordinary least squares model produces unbiased estimates even if the data are skewed [135,136]; however, additional estimation methods (eg, generalized linear models) and different uncertainty methods (eg, parametric and nonparametric bootstrapping) will be explored to facilitate investigation of the impact of various cost assumptions.

As a secondary cost objective, we will compare the cost and quality-adjusted life years (QALYs) between the two groups using the net benefit regression framework (see Table 3). QALY is a preference-based utility measure of HRQL, as perceived by the patient, that incorporates both length of life and quality of life into a single measure [137,138]. We aim to determine the incremental net benefit of interventions versus usual care. To estimate QALYs gained, we will convert SF-12v2 data collected to utility scores using a validated algorithm. We will also estimate the incremental cost per QALY gained. A cost-effectiveness acceptability curve (95% CI) will be used to characterize the uncertainty of our findings [139].

#### Uptake of Technology

Data on uptake of the SMArTVIEW intervention will be used to explain differences in the outcome measures, determine patterns of use to predict outcomes, and identify users who may require escalated care. Session frequency (ie, times the technology is accessed) and session length (ie, length of time users interact with the technology) [140] will be determined via daily metrics of both device and application use. During Phase 1, mPath will identify all key actions of SMArTVIEW to generate a template for relevant data collection at a granular, individual user level.

**Table 3 table3:** Summary of outcomes, hypotheses, measures, and methods of analysis.

Analyses	Outcome	Hypothesis	Outcome measure	Method of analysis
**Primary outcome**				
	8-week worst postop pain intensity *upon movement* score in the past 24 hours	Intervention > control	Measured by Brief Pain Inventory-Short Form (BPI-SF^a^)	Linear mixed model or nonlinear mixed models (if assumptions of normality are violated)
**Secondary outcome**				
	Functional status	Intervention > control	Short-Form 12 version 2	Linear mixed model or nonlinear mixed models (if assumptions of normality are violated)
	Depressive symptom scores	Intervention > control	Five-question version of the Geriatric Depression Scale	Linear mixed model or nonlinear mixed models (if assumptions of normality are violated)
	Postop complications related to hemodynamic compromise	Intervention > control	Myocardial infarction and stroke	Nonlinear mixed models
	Other relevant postop complications	Intervention > control	Surgical site infection, presence of CPSP^b^	Nonlinear mixed models
	Heath service utilization-related cost	Intervention > control	Linked with health administrative Institute for Clinical Evaluative Sciences data repository	Linear mixed model or nonlinear mixed models (if assumptions of normality are violated)
	Patient-level cost of recovery	Intervention > control	Ambulatory and Home Care Record	Linear mixed model or nonlinear mixed models (if assumptions of normality are violated)

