### Data Analyses

#### Primary Analyses

Table 3 summarizes all data analyses. Using the intent-to-treat principle [128], all patients will be included in the final analysis and according to the group to which they were randomly allocated. Descriptive statistics will be used to describe sample characteristics using measures of central tendency and dispersion for continuous factors, and frequencies and proportions for categorical factors. A two-sided significance level of .05 will be used for all inferential analyses. Statistical methods used will depend on the type and distribution of data for the outcome variable under study. If outcome data meet requirements for parametric statistics, a linear mixed model [129] will be used to assess the effects of the intervention on the primary outcome. An a priori contrast of the weekly average worst score for the BPI-SF numeric rating scale *upon movement* (previous 24 hours) will be used to evaluate the primary endpoint of acute postop pain at 30 days postrandomization.

Linear mixed models, using an autoregressive [130] covariance structure—allowing for correlations between measurements to decline as they are further apart in time—will be used to evaluate within-patient variation in patient-reported outcomes over 12 months of follow-up. Linear mixed models are a flexible and powerful approach to the analysis of data with a complex variance structure, such as correlated data [129-131]. Unlike traditional repeated-measures designs, these models do not require complete data on each patient and have increased statistical power [132]. Nonlinear mixed models will be used in the following cases: (1) if continuous data violate assumptions of normality [132] and (2) for categorical secondary outcomes (eg, adverse event). Chi-square tests of association will be used to assess the association between categorical secondary outcomes identified in the administrative data and intervention. Given that the data is derived from an RCT, complex modeling for these outcomes will not be performed, as potential confounders are considered to be adjusted for in the design. Finally, we will examine patterns of missing data and determine demographic and/or clinical characteristics that are related to missing data at each time point, and the potential impact on the primary findings.

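### The two cost outcomes carry two analysis rules: Table 3 leaves the linear model when normality fails, the economic section targets mean cost under skew, and neither is said to govern

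*Protocol article*

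**What the plan says.** **Table 3, secondary outcomes.** There are two cost rows. The first is health service utilization cost, whose measure is "Linked with health administrative Institute for Clinical Evaluative Sciences data repository". The second is patient-level cost of recovery, measured by the Ambulatory and Home Care Record (AHCR). Both have the same method entry: "Linear mixed model or nonlinear mixed models (if assumptions of normality are violated").

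**Primary Analyses.** This section presents Table 3 as the summary of every data analysis. It lists the cases in which nonlinear mixed models will be used, the first being "1) if continuous data violate assumptions of normality". Costs are not exempted.

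**Cost-Effectiveness Analyses.** Total cost is the dependent variable, "using a regression model to estimate the difference in expected health care cost between the two groups". On skew the section says: "In theory, an ordinary least squares model produces unbiased estimates even if the data are skewed". It continues that "additional estimation methods (eg, generalized linear models) and different uncertainty methods (eg, parametric and nonparametric bootstrapping) will be explored", and that "the regression model will adjust for potential confounding variables". It adds a net benefit regression on cost and QALYs. It refers the reader to Table 3 for both the two-perspective analysis and the net benefit comparison.

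**Follow-Up.** The AHCR is collected by telephone at 3, 6, 9 and 12 months, so patient-level cost is a repeated measure.

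**The concern.** The two places treat skewed costs differently. In Table 3 and Primary Analyses, failure of normality is the reason to leave the linear model. In the economic section, skew is not a reason to abandon a model for mean cost. An analyst who follows the article literally cannot tell which rule applies to the same outcomes.

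The trigger is likely to be met. Costs cannot be negative, and a minority of patients have an expensive event. The introduction cites a 30-day readmission rate of 18.7% after cardiac surgery.

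Incremental cost and net benefit both need the difference in arithmetic means, because only the mean multiplied by the number of patients gives the total spend. A nonlinear mixed model may return a ratio, or an effect conditional on a patient's random effect, and neither is that quantity in general. With no stated precedence, a distributional check on the trial data could decide which cost estimate is reported.

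**Working it through.** **1. The passages side by side**

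| | Table 3 cost rows and Primary Analyses | Cost-Effectiveness Analyses |
|---|---|---|
| Target | Not stated | Difference in expected (mean) cost |
| Default model | Linear mixed model | Regression on total cost |
| If data are skewed | Switch to nonlinear mixed model | Least squares described as still unbiased; GLM and bootstrap explored as well |
| Link, distribution, effect scale | Not stated for the nonlinear model | Cost scale, as a difference |

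The conflict lies in the second and third rows of text and needs no assumption. The linear version of Table 3 would be close to the economic analysis; the nonlinear version need not be.

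**2. The plan's own figures**

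The article gives no mean, spread or power for costs, so there is no cost figure to reproduce. The group sizes used below follow from Sample Size: 64 / 0.9 = 71.1, so 72 per group at one site, and 144 per group over both. The administrative cost data are Canadian only, so 72 per group applies to that row.

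**3. When direction could differ (all cost inputs assumed)**

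Let costs be log-normal with log-SD s_c (control) and s_t (intervention), and let GMR be the geometric mean ratio, intervention to control.

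- Mean ratio = GMR × exp((s_t² − s_c²)/2).
- With GMR above 1, the mean ratio falls below 1 only if GMR < exp((s_c² − s_t²)/2).

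| s_c / s_t | Upper limit of GMR for a reversal |
|---|---|
| 1.0 / 1.0 | 1.00 (no true reversal) |
| 1.0 / 0.8 | 1.20 |
| 1.2 / 1.0 | 1.25 |
| 1.2 / 0.8 | 1.49 |
| 1.4 / 0.8 | 1.93 |

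Example: control geometric mean 10,000, s_c = 1.2, s_t = 0.8, GMR 1.2.

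- Control mean: 10,000 × exp(0.72) = 20,544.
- Intervention mean: 12,000 × exp(0.32) = 16,526.
- Difference −4,019 before rounding, ratio 0.80, against a log-scale ratio of 1.20.

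Share of simulated trials in which the mean difference and the log-scale estimate have opposite signs, at GMR 1.2:

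| s_c / s_t | 72 per group | 144 per group |
|---|---|---|
| 1.0 / 1.0 | 14% | 9% |
| 1.0 / 0.8 | 38% | 45% |
| 1.2 / 0.8 | 68% | 83% |

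With equal spread, disagreement is sampling noise and shrinks with size. With unequal spread it need not shrink.

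**4. A mechanism that makes spread differ**

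Assume other cost is log-normal with median 2,000 and a readmission costs 10,000 on average. Control readmission is 18.7%.

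- Intervention adds 500 and readmission falls to 12%: mean difference 500 − 0.067 × 10,000 = −170.
- Intervention adds 800 and readmission falls to 10%: mean difference 800 − 0.087 × 10,000 = −70.

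The geometric mean ratio depends on spreads that the article does not give. Varying the log-SD of other cost over 0.3 to 1.5 and of readmission cost from about 0 to 1, it is 1.09 to 1.28 in the first case and about 1.18 to 1.43 in the second. The mean falls while the log-scale ratio exceeds 1 throughout.

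**5. An actual mixed model**

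A gamma log-link random-intercept model was fitted to four repeated costs per patient, with true conditional ratio 1.2 and 40 simulated trials per setting.

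- Between-patient SD 1.2 / 0.8: median model ratio 1.16 to 1.18 against a ratio of mean totals of 0.84 to 0.85. Directions were opposite in 50% of trials at 72 per group and 80% at 144.
- Equal SDs of 1.0: opposite in 18% and 8%.

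**6. When the problem goes away**

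An unadjusted gamma log-link GLM without random effects reproduces the raw mean ratio exactly. In one sample both were 0.581 while the geometric mean ratio was 1.23. The issue is therefore the quantity reported, not non-normal models as such.

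**The case against.** **The economic section is not a rigid rule for least squares.** Its statement is qualified as theoretical, and other estimators are to be explored. This stands: the estimator is partly open. The target, the difference in expected cost, is not.

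**The nonlinear mixed model's link and effect scale are unstated, and an analysis plan commonly supplies them.** It may mean a generalized mixed model, close to the GLMs that the economic section allows. This also stands, and it limits what can be said about direction. It does not resolve which of the two stated rules applies.

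**The Table 3 rows may be ordinary secondary comparisons, separate from the economic evaluation.** The table is a summary, and as shown it has no row for net benefit. Nothing says that a Table 3 mixed model feeds incremental cost or net benefit. This is possible, but the economic section sends the reader to Table 3, the only cost rows there carry the trigger, and the cost sources overlap. If two analyses are meant, the article needs to say so.

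**A mixed model is legitimate for the repeated AHCR costs.** Agreed, and the fix keeps it.

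**Stronger readings.** A reader might infer that the plan will reverse its cost conclusion, or that it commits to a log-scale comparison. The documents support neither: no log-scale or geometric-mean analysis of cost is stated, and no cost distribution is given.

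**Conclusion.** The inconsistency holds on the text alone. The same two cost outcomes have a normality-triggered switch to nonlinear mixed models in one place and a mean-cost regression that tolerates skew in another, with no precedence stated.

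That the trigger would probably fire is a judgement about cost data in general. That the resulting estimate need not be an arithmetic mean difference follows from the model class.

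A difference in direction is conditional. It rests on assumed cost distributions, on spread that differs by arm, and on a result read on a log or patient-specific scale. With equal spread, or with the result converted back to a population mean cost difference, direction is preserved in expectation, though significance can still differ. The only document figure in the cost illustrations, apart from group sizes, is the 18.7% readmission rate, which is for 30 days after cardiac surgery only.

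Costs are secondary outcomes, so the pain conclusion is untouched. The correction should be made because the cost results depend on it and it is nearly free.

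**What to change.** 1. In both cost rows of Table 3, replace the method entry with the economic section's analysis as the governing one: arithmetic mean difference in total cost by ordinary least squares, or by a GLM with predictions returned to the cost scale, with a bootstrap confidence interval. Remove the normality trigger from these rows.
2. In Primary Analyses, exempt the cost outcomes from the rule that sends non-normal continuous data to nonlinear mixed models. Editing the table alone would leave the conflict in place.
3. Keep any mixed model of the repeated AHCR costs as supportive, and report it as a population mean cost difference.

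The cost is minor text edits in two places and slightly more analysis work. No added patients, visits or data are needed.

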**Subgroup outcomes**				
	All outcomes	Effect will differ by gender (male versus female)	Worst postop pain intensity *upon movement* score in the past 24 hours measured by BPI-SF numeric rating scale	Interaction test
	All outcomes	Effect will differ by GREP^c^ scores (low versus high)	Worst postop pain intensity *upon movement* score in the past 24 hours measured by BPI-SF numeric rating scale	Interaction test

^a^BPI-SF: Brief Pain Inventory-Short Form.

^b^CPSP: chronic postsurgical pain.

^c^GREP: Gender Role Expectations of Pain.

### Qualitative Analyses

#### Qualitative Description

Data will be digitally recorded, transcribed verbatim, and managed in NVivo 11 (QSR International). Concepts that relate to the usability and value of the intervention will be coded [141] and reviewed by investigators to resolve differences and minimize biases [141]. Revisions to the interview guide and codebook will reflect emerging themes.

#### Critical Qualitative Analysis

To reveal the ethical, legal, and social implications of the intervention, we will apply methods used successfully in previous research [142]. Following this, data will be re-examined using four bioethical concepts—relational autonomy, care, social justice, and privacy—to draw out the normative implications of the intervention which are sensitive to ethical issues common to at-home care for seniors [143]. A *retroductive* process will be used that involves moving between observations and concepts and allows the interplay between individuals’ lives and larger social and contextual forces to be understood [144,145]. The four concepts will not be used simply as containers to categorize data uncritically to aid in the social and ethical analysis of the data. Rigor will be maintained by keeping a reflexive journal and audit trail [141] and ensuring that the purpose of the research, theoretical assumptions, and method of data analysis are congruent [146].

### Controls for Bias

To limit sampling bias, a recruitment schedule randomly generated to ensure representation from each surgical group will be used. Contamination should not exist between groups as we will control who interacts with the SVN and intervention features. Those allocated to the intervention group will be asked not to share their tablets or demonstrate application features to any peers assigned to the control group. To evaluate cointervention, we will track participant receipt of any monitoring or recovery support-related interventions, outside of expected usual care up to 8 weeks postoperation. RAs responsible for outcome data collection will be separated from randomization procedures, will have no permitted access to IWRS, will not be involved in intervention delivery, and will be blinded to group allocation. An event adjudication committee responsible for adjudication of all clinical outcome data will be blinded to randomized allocation. The team has extensive experience with assiduous follow-up procedures to minimize losses to follow-up.

### Knowledge Translation

Integrated knowledge translation strategies will continue to involve stakeholder groups during the project. As part of integrated and end-of-grant knowledge translation, stakeholders will assist in interpreting findings, identifying key results, and reviewing and revising the end-of-grant knowledge translation plan at a final meeting for review of investigator results. End-of-grant knowledge translation goals—generate interest, discussion, and awareness; impart knowledge; and inform research—will be addressed via tailored implementation strategies.

## Results

Study start-up is underway and usability testing is scheduled to begin in the fall of 2016.

## Discussion

THE SMArTVIEW, CoVeRed innovation community brings together an international, dedicated group of well-known clinical and eHealth researchers; health economists; clinicians; administrators; patient representatives; engineers, information technology, and clinical informatics experts; as well as leaders in the arenas of health policy, big data and data aggregation, bioethics, knowledge translation, and privacy. Collectively, we possess the requisite skills, experience, and track record to execute the proposed evaluation, disseminate what we learn, and plan for diffusion of innovation.

We are actively engaged in systems integration and change management at both study sites. As a result of planned, shared stewardship of our vision, we have fostered a milieu of co-ownership and investment in SMArTVIEW usability and effectiveness testing. With respect to end-user engagement, we understand well from experience that innovation is not a linear process. We are committed to recursive coinnovation between “solutioner” and end users. Hence, corefinement of SMArTVIEW— via usability testing in context—was a key objective identified during team debriefing, following our patient journey mapping exercise. Akin to the use of “experimentation suites” in the industry sector, our process, as outlined within the Usability Testing section, will be to immerse with participants in high-fidelity rehearsal of SMArTVIEW activities in order to uncover ways we can refine our processes to optimize the experience of recovery for seniors following CaVS. Our team, including patient representatives, is organized into both content and governance committees (see Table 4).

In collaboration with our industry partners, Canadian and UK hospital sites, we are confident that we have the experience, expertise, infrastructure, and support to realize THE SMArTVIEW, CoVeRed. A copy of our Canadian Institutes of Health Research (CIHR) reviews can be found in Multimedia Appendix 2.

**Table 4 table4:** SMArTVIEW^a^ team committees.

Committee type	Committee name
**Content**	
	Clinical Transformation/Change Management
	Clinical Monitoring
	Patient Engagement and Experience
	Economics
	Knowledge Translation
	Systems Integration
	Self-Management
	Clinician and SVN^b^ Training
	Ethics
**Governance**	
	Project Office Operations
	International Operations
	Steering
	Outcomes Adjudication
	External Safety
	Efficacy and Monitoring
	Substudy and Publications

^a^SMArTVIEW: Self-MAnagemenT—VIsion for patient EmpoWerment.

^b^SVN: SMarTVIEW Nurse.

## Appendix

Multimedia Appendix 1 Approach to meta-analysis.

Multimedia Appendix 2 Canadian Institutes of Health Research (CIHR) reviews.

## Abbreviations

AHCR: Ambulatory Home Care Record
BPI-SF: Brief Pain Inventory-Short Form
CAM: Confusion Assessment Method
CARD: Cardiac
CaVS: cardiac and vascular surgery
CIHI: Canadian Institute for Health Information
CIHR: Canadian Institutes of Health Research
CPSP: chronic postsurgical pain
eCC: eCare Coordinator
ECG: electrocardiogram
eTrAC: Transition to Ambulatory Care
EWS: early warning score
GDS-5: five-question version of the Geriatric Depression Scale
GREP: Gender Role Expectations of Pain
HOPE: Help to Overcome Problems Effectively
HR: hazard ratio
HRQL: health-related quality of life
ICU: intensive care unit
iHOPE: Internet-based Help to Overcome Problems Effectively
IWRS: Interactive Web Randomization System
MoHLTC: Ministry of Health and Long-Term Care
N/A: not applicable
PCI: percutaneous coronary intervention
POISE: PeriOperative ISchemic Evaluation
postop: postoperative
PRAS: pain relief after surgery
PROMIS: Patient-Reported Outcomes Measurement Information System
QALY: quality-adjusted life year
RA: research assistant
RCT: randomized controlled trial
SF-12v2: Short-Form 12 version 2
SpO2: peripheral oxygen saturation
SSI: surgical site infection
SVN: SMArTVIEW Nurse
THE SMArTVIEW, CoVeRed: TecHnology-Enabled remote monitoring and Self-MAnagemenT—VIsion for patient EmpoWerment following Cardiac and VasculaR surgery
